| Investigations regarding the safety of the treatment: | 
 
1. clinical laboratory tests
 
2. recording of adverse events over the entire period
 
3. recording of vital signs and physical examination at each visit
 
                                                                                                                                                                                                                                                                                                                                                                                                                                                                                                                                                                                                                                                                                                                                                                                                                                                                                                                                                                                                                                                                                                                                                                                                                                                                                                                                                                                                                                                                                                                                                                                                                                                                                                                                                                                                                                                                                                                                                                                                                                     |

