## 1.5 PERIOD AND TIMELINES

Treatment period: 8 weeks

Primary endpoint: at Week 12

Follow-Up Period in the core study period: 28 weeks

Total study duration per subject in the core study period: 40 weeks (4 weeks screening, 8 weeks treatment, 28 weeks follow-up)

First patient first visit to last patient first visit: 15 months

Follow-up in the long-term extension (LTE) observational period: 48 weeks

Total study duration: 88 weeks (40 weeks in the core study and 48 weeks in the LTE observational period)

Interim analysis: after the 5th patient at Week 12

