## 5.4 PROHIBITIONS AND RESTRICTIONS

Potential subjects must be willing and able to adhere to the following prohibitions and restrictions to be eligible for participation:

- refer to Section 6.6 PROHIBITED THERAPY for additional details regarding therapies that are prohibited and restricted during the study.
- agree to follow all requirements that must be followed during the study as described in the Inclusion and Exclusion Criteria, Sections 5.1. and 5.2 (e.g. contraceptive requirements).
- agree to avoid excess exposure to natural or artificial (e.g. tanning beds, phototherapy) sunlight. In addition, it is advised that subjects maintain their typical use of sun protective measures (such as a hat, sunglasses, protective clothing, sunscreen). The time period for this requirement is from the start of screening until the last dose of study agent has been received.
- use of additional immunosuppressants or immunomodulators, other than those explicitly allowed in the inclusion/exclusion criteria (Section 5.1 and 5.2), are prohibited including but not limited to those listed in Section 6.9.
- must agree not to receive a live virus or live bacterial vaccination during the study.
- subjects must also agree not to receive BCG vaccination for 12 months after last dose of study agent, or any other live vaccine for 16 weeks after receiving the last administration of study agent.
- must agree not to receive an investigational medical device or an investigational drug other than study agent for the duration of this study.
- Skin concealers or topical tan preparations or nonpermanent tattoos should be avoided.
- within 48 hours before a study visit due to their potential to obscure skin disease activity.
- subjects should avoid use of any wigs or hair attachments that cannot be readily removed for scalp examination.
- Women of child bearing potential (WOCBP) must use a sufficient contraception during the time of study treatment, and 20 weeks thereafter. If the subject withdraws from the study prematurely, the 20 weeks must also be guaranteed.

Highly effective methods of contraception include:

- combined (estrogen and progestogen containing) hormonal contraception associated with inhibition of ovulation:
  - oral
  - intravaginal
  - transdermal
- progestogen-only hormonal contraception associated with inhibition of ovulation:
  - oral
  - injectable
  - implantable
- intrauterine device (IUD)
- intrauterine hormone-releasing system (IUS)
- bilateral tubal occlusion

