## 7 STUDY EVALUATIONS

### 7.1 STUDY PROCEDURES

The current SARS-CoV-2 pandemic leads to changes from the routine procedures of study visits and to the following regulations: Patients must undergo a SARS-CoV-2 rapid test prior to each study visit (either to bring a test no older than 24 hours or a rapid test will be performed on site). Depending on the SARS-CoV-2 incidence rate and the current operating guidelines, it must be weighed whether the currently prevailing risk of infection for the patient is increased by an on-site visit. This is the case for all patients not fully vaccinated against SARS-CoV-2. For these patients, visits not including study drug administration (weeks 16 through 32) may be replaced by remote (video) visits. SARS-CoV-2 infection of study participants will automatically lead to study drug discontinuation but not necessarily to study termination. Rather, the follow-up phase can be continued once quarantine/COVID-symptoms/SARS-CoV-2 PCR positivity have resolved.

The study-specific procedures for each patient visit at the study site are shown in the following table.

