### 8.2 DISCONTINUATION OF STUDY TREATMENT

A participant will not be withdrawn from the study if he or she has to discontinue study agent before the end of the treatment regimen.

A subject's study agent must be discontinued if:

- Inclusion or exclusion criteria violation was noted after the subject started study drug, when continuation of the study drug would place the subject at risk as determined by the Investigator
- the Investigator, sponsor, and/or medical monitor believes that for safety reasons or tolerability reasons (e.g. adverse event), or due to severe, unstable, or rapidly progressive SLE disease activity, it is in the best interest of the subject to discontinue study agent.
- The subject (or the subject's legally acceptable representative) withdraws consent for administration of study drug.
- the subject develops study agent hypersensitivity (e.g. anaphylaxis, angioedema) reaction that is reported as serious or severe.
- the participant develops a serious opportunistic infection or SARS-CoV-2 infection confirmed by positive PCR-test (the follow-up phase can be continued once quarantine/COVID-symptoms/SARS-CoV-2 PCR positivity have resolved).
- if a new immunomodulator that is permitted per-protocol is initiated, then a participant will be considered a treatment failure but will not need to be withdrawn from the study.
- Occurrence of serious adverse events which are not compatible with the further administration of the study drug.

It is recommended that follow-up visit should be continued although patients might have discontinued study drug or had temporarily halt of study drug.

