In the event of withdrawal from the study through a decision by the sponsor, the investigating doctor or the study participant, the early termination visit will be carried out (which is equivalent to the visitation procedures at Week 36 of the core study period or Week 84 in the LTE observational period). Furthermore, a follow-up visit will be held, recording the adverse outcomes with an interval of 8 weeks after the last administration of the study drug (final study visit). The participants in the study will be transferred for further rheumatological treatment to the respective responsible/referring treatment institution after the study has been concluded.

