### 10.5 PROCEDURES

The sponsor respectively the principal investigator is responsible for adequate reporting of adverse events/SUSARs to the regulatory authorities and to the competent independent ethics committee.

All adverse events, whether serious or not, are recorded from the time of receipt of the first signed and dated ICF until the completion of the last follow-up visit of the last patient. Serious adverse events, including those occurring until the end of the follow-up observation period following the last dose of the study drug must be reported using the Serious Adverse Event Form. The sponsor will include in the analysis all safety information reported by the investigator within the period specified in this protocol. If a serious adverse event occurs, then this is to be reported to the sponsor within 24 hours. In this monocentric study, this is determined in a way that each sub-investigator must contact the principal investigator of this clinical trial within 24 hours. The investigating physician will evaluate and record

every serious adverse event in detail, with at least the patient number, attribution (causal relationship) the study drug, degree of severity, start and end dates and medication, as well as other therapies for the treatment of the adverse event being recorded. In addition, the age, alternative etiology, relevant previous and concomitant diseases, concomitant medication/treatments will be recorded, together with any laboratory results of relevance to this event.

If adverse, serious and at the same time unexpected drug interactions (SUSAR) occur, the sponsor (simultaneously principal investigator) will inform all participating sub-investigators without delay. Furthermore, the responsible ethics committee, authority (PEI) and manufacturer of the study drug will be informed within the regular periods of time.

All adverse events, regardless of their severity or suspected association with the study drug must be recorded in the source document and in the CRF using medical terminology. Whenever possible, diagnoses should be made (rather than documenting symptoms). Investigators must provide the following information in the source document and CRF:

- Start date
- Stop date (if applicable)
- Assessment of the relationship of the adverse event to the study therapy,
- the degree of severity and
- all actions required for the adverse event
- IMP batch number

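### For fully dosed patients withdrawn before Week 28, planned contact ends up to 12 weeks before the 20-week contraception period does

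*Protocol*

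**What the plan says.** **Withdrawn patients.** Section 8.3 applies when the sponsor, the investigator or the participant decides on withdrawal. It plans an early termination visit with the Week 36 procedures (Week 84 in the extension), and a further visit for "recording the adverse outcomes with an interval of 8 weeks after the last administration of the study drug (final study visit". Nothing is planned after that.

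**Contraception.** In section 5.4, women of childbearing potential "must use a sufficient contraception during the time of study treatment, and 20 weeks thereafter", and the same bullet continues: "If the subject withdraws from the study prematurely, the 20 weeks must also be guaranteed". Section 5.1 binds men for at least 20 weeks after the last dose but does not mention withdrawal.

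**Serious adverse events.** Section 10.5 says that serious adverse events "including those occurring until the end of the follow-up observation period following the last dose of the study drug must be reported". Section 1.5 gives "Follow-Up Period in the core study period: 28 weeks". Section 10.5 does not say which end applies to a patient who has left the study.

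**Who is not affected.** Section 8.2 keeps patients who only stop the drug: "A participant will not be withdrawn from the study if he or she has to discontinue study agent". Section 7.6.7 follows a known pregnancy to its outcome even after the patient has left.

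**The concern.** Section 5.4 addresses withdrawn patients directly and asks that their 20 weeks be guaranteed, while section 8.3 ends planned contact with them earlier. No visit or call in 8.3, 7.6.7, 10.5 or 10.6 bridges the interval. Section 10.6 requires a pregnancy to be reported within 24 hours of notification, so that duty starts only once the site has been told. A new pregnancy or serious adverse event in the interval would reach the site only if the patient reported it.

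The patients concerned are not only those who have turned away from the trial. Section 8.3 makes withdrawal automatic for events such as confirmed thrombosis or embolism, gastrointestinal perforation, malignancy and active neuropsychiatric lupus. Such patients can usually still be reached, yet they get less planned safety follow-up than patients who stay. With 10 patients enrolled, one unreported event would matter to the safety description.

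**Working it through.** **Inputs.** Visit days from the Time and events schedule: Week 8 (eighth dose) = Day 49, Week 12 = 77, Week 16 = 105, Week 20 = 133, Week 24 = 161, Week 28 = 189, Week 36 = 241. Interval to the final visit: 8 weeks = 56 days (8.3). Contraception period: 20 weeks = 140 days (5.4, 5.1). Visit windows are ignored, and the end of treatment in 5.4 is taken as the last dose.

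**Check against the protocol's own figure.** Section 3.2.1 places Week 12 four weeks after the last injection: (77 − 49)/7 = 4. The anchor reproduces.

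**Formulas.** With last dose on Day D and early termination on Day W:
- last planned contact L = max(W, D + 56)
- weeks without planned contact = max(0, D + 140 − L)/7

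**Eight doses (D = 49).** Final visit: 49 + 56 = Day 105, Week 16. End of the 20 weeks: 49 + 140 = Day 189, Week 28.

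| Withdrawn | Last planned contact | Weeks without planned contact | Adverse-event visits of retained patients in that time |
|---|---|---|---|
| by Week 16 | Day 105 | (189 − 105)/7 = 12 | 3 (Days 133, 161, 189) |
| at Week 20 | Day 133 | (189 − 133)/7 = 8 | 2 (Days 161, 189) |
| at Week 24 | Day 161 | (189 − 161)/7 = 4 | 1 (Day 189) |
| Week 28 or later | Day 189 or later | 0 | 0 |

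**Fewer doses.** The maximum stays at 20 − 8 = 12 weeks on earlier dates. After four doses (D = 21) the final visit is 21 + 56 = Day 77 and the period ends on 21 + 140 = Day 161: (161 − 77)/7 = 12.

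**With a contact at D + 140.** The time without planned contact before the end of the 20 weeks is split by nothing further, but the period now closes with a contact: no part of it is left unasked about, so the uncovered remainder is 0.

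**Against 10.5.** If the duty to report serious adverse events runs to Week 36 for a withdrawn patient, a call on Day 189 still leaves 241 − 189 = 52 days. If it ends at the visit that 8.3 calls final, there is no shortfall against 10.5.

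**The case against.** The strongest reply is that two separate rules are being joined. The 8 weeks concern adverse events and the 20 weeks concern contraception. The sentence about guaranteeing the 20 weeks stands in a list of what patients must be willing to do, so it binds the patient and promises no contact by the sponsor. The protocol also supports contraception by other means: counselling and pregnancy reporting (10.6) and follow-up of known pregnancies (7.6.7). Retained patients have no scheduled pregnancy test between baseline and Week 36 either. Patients who are lost, have died or refuse contact gain nothing.

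All of this stands, and it rules out calling the plan a breach. It does not remove the practical point: the protocol wants the precaution kept after withdrawal and plans nothing to support it in patients who can still be reached.

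Several stronger readings are tempting and not supported:
- **That adverse events must be collected for 20 weeks.** No section makes the 20 weeks an adverse-event window.
- **That the 5.4 clause covers everyone.** Its extension to withdrawal is written for women of childbearing potential only.
- **That 20 weeks is also the live-vaccine limit in 5.4.** That section gives 16 weeks (12 months for BCG); exclusion criterion 9 in 5.2 gives 20. Against 16 weeks the maximum would be 16 − 8 = 8 weeks.
- **That one call fully meets 10.5.** It may leave 52 days, as shown.
- **That 7.1 accepts remote contact in general.** Its statement that "visits not including study drug administration (weeks 16 through 32) may be replaced by remote (video) visits" is a pandemic measure for patients not fully vaccinated against SARS-CoV-2, and it concerns video visits.
- **That late or extension withdrawals lose a visit.** For a fully dosed patient leaving after Week 16 the 8-week date has passed, but the Week 16 visit fell on it.

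**Conclusion.** The point holds as a minor improvement to a stated rule. For withdrawn patients, up to 12 weeks of the 20-week contraception period have no planned contact, falling to none for fully dosed patients who leave at Week 28 or later. The figures rest on the scheduled visit days and on eight doses; with fewer doses the maximum is the same and the cut-off comes earlier.

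The number of patients affected cannot be derived from the protocol and is probably small. The 50% drop-out in section 9.2 is a conservative planning assumption and does not forecast withdrawals before Week 28. No endpoint, estimate or efficacy analysis is affected.

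**What to change.** In section 8.3, keep both existing visits and add one telephone contact 20 weeks after the last dose for patients who withdraw earlier and have not refused contact. It should ask about pregnancy, contraception, and serious and other adverse events. Priority goes to women of childbearing potential and to men bound by the 20-week rule in 5.1.

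In section 10.5, state that for withdrawn patients collection of serious adverse events ends at this contact, or at the early termination visit if that is later. This settles which end applies, and it also covers extension withdrawals.

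The cost is an amendment and at most one call per early withdrawn patient by existing site staff, so at most 10 calls if all 10 patients left early. No sampling or procedure is added. A call can ask and remind, but it cannot prove contraception.

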## 8.4 WITHDRAWAL FROM THE USE OF RESEARCH SAMPLES

Patients withdrawn from this study will have the following two options regarding the research samples:

- Collected samples will be stored and used for analysis in compliance with the subject's original informed consent form.
- A patient may withdraw his or her consent to the research samples analysis. In this case, the samples will be destroyed, and no further testing will occur. To initiate the sample destruction process, the investigator must notify the principal investigator of the withdrawal of consent for the optional research samples and request sample destruction. The principal investigator will contact the corresponding laboratory representative to initiate destruction of blood samples. If requested by patient, the investigator will receive written confirmation from the laboratory that the samples have been destroyed and can hand over this to the patient.

## 9 STATISTICAL METHODS

### 9.1 SUBJECT INFORMATION

#### 9.1.1 DEMOGRAPHICS AND BASELINE CHARACTERISTICS

For all subjects who receive at least 1 dose of daratumumab, descriptive statistics on demographics and baseline disease characteristics will be provided. Descriptive statistics (mean, standard deviation, median, and range) will be provided for the subjects' age, weight, height, anti-dsDNA antibody titers, SLEDAI-2K score, PGA score, CLASI, CDAI, SF-36 and FACIT-Fatigue. Subject sex, race, concomitant medication use, number of BILAG A or BILAG B criteria, positivity for ANA, anti-dsDNA antibodies, or other autoantibodies, number with low complement C3 or C4 levels will be summarized as frequency distributions.

### 9.1.2 DISPOSITION INFORMATION

Disposition information will be based on all subjects who receive at least 1 dose of daratumumab. The number of subjects who discontinued daratumumab and the reason for discontinuation as well as those who terminated the study and reason for termination will be summarized.

### 9.1.3 TREATMENT COMPLIANCE

Daratumumab will be administered as subcutaneous injection by an authorized and qualified staff member and the details of each administration will be recorded in the CRF including date, start time for injection. Compliance with the treatment assignments will be controlled by the study site personnel. Subjects will be required to record in their subject diaries, all doses of study agent that are administered at home.

### 9.1.4 EXTENT OF EXPOSURE

The number of subjects exposed to daratumumab, the number of administrations of study agent, and cumulative dose of daratumumab will be summarized.

### 9.1.5 PROTOCOL DEVIATIONS

Major protocol deviations will be tabulated in the following categories:

- Subjects who “entered but did not satisfy entry criteria” or “received wrong treatment” or
- “incorrect dose” or “developed withdrawal criteria but not withdrawn” or “received a disallowed concomitant medication” and “other study procedures”.

### 9.1.6 PRIOR AND CONCOMITANT MEDICATIONS

Prior and concomitant medication use for active SLE will be summarized at each study visit. Subjects initiating new medications or changes in dose (increasing or decreasing) of medication for active SLE during the study will be summarized at each study visit. Subjects with increases in medication will be listed. Prior and concomitant medications will be coded according to the World Health Organization (WHO) encoding dictionary, and the number and percent of subjects receiving each medication in each treatment group will be summarized by Level 3.

## 9.2 SAMPLE SIZE DETERMINATION

The primary objective of this exploratory study is to evaluate whether treatment with the anti-CD38 antibody daratumumab is associated with a significant reduction of pathogenic serum anti-dsDNA antibodies in patients with moderate to severe SLE. Results from two patients treated with daratumumab in our institution (compassionate use) resulted in a mean reduction of anti-dsDNA antibodies by 250 IE/ml (SD 121) what corresponds to a reduction of about 50% at 90 days follow-up after first dose of daratumumab. It yields an effect size of 2.1. A sample size of 5 patients is necessary to show a significant reduction in anti-dsDNA antibodies by a two-tailed Wilcoxon signed-ranked test for matched pairs between baseline and the 12-week follow-up visit, assuming a statistical power of 80% and a type one error rate of 5%. We conservatively assume a drop-out rate of 50%. Therefore, a total of 10 patients will be enrolled in this exploratory study. Sample size calculation was performed with G\*Power version 3.1.9.2.

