| 
Sample size calculation and statistical evaluation:
 | 
Results from two patients treated with daratumumab in our institution (compassionate use) resulted in a mean reduction of anti-dsDNA antibodies by 250 IE/ml (SD 121) what corresponds to a reduction of about 50% at 90 days follow-up after first dose of daratumumab. It yields an effect size of 2.1. A sample size of 5 patients is necessary to show a significant reduction in anti-dsDNA antibodies by a two-tailed Wilcoxon signed-ranked test for matched pairs between baseline and the 12-week follow-up visit, to achieve statistical power of at least 80% assuming a type
                                                                                                                                                                                                                                                                                                                                                                                                                                                                                                                                                                                                                                                                                                                                                                                                                                                                                                                                                                                                                                                                                                                                                                                                                                                                                                                                                                                                                                                                                                                                                                                                                                                                                     |

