|                                                                    |                                                                                                                                                                                                                                                                                                                                                                                                                                                                                                                                                                                                                                  |
|--------------------------------------------------------------------|----------------------------------------------------------------------------------------------------------------------------------------------------------------------------------------------------------------------------------------------------------------------------------------------------------------------------------------------------------------------------------------------------------------------------------------------------------------------------------------------------------------------------------------------------------------------------------------------------------------------------------|
| Sample size calculation and statistical evaluation (cont.): | 
one error rate of 5%. We conservatively assume a drop-out rate of 50%. Therefore, a total of 10 patients will be enrolled in this study. Sample size calculation was performed with G*Power version 3.1.9.2.
 
Primary endpoint analysis of the core study
 
The median and interquartile range is reported for anti-dsDNA antibody titers at baseline and at Week 12, i.e. 4 weeks after the last daratumumab injection. No confirmatory hypothesis test will be performed due to the exploratory study design. 95% confidence intervals are calculated for the median change from baseline to Week 12.
 |

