## 7.5 PHARMACOKINETICS

Daratumumab concentrations will be analyzed after the end of the study from cryopreserved serum samples, which had been obtained at Week 9 (one week after the last daratumumab injection), under the premise that the primary endpoint will be achieved. For this reason, a serum sample (5ml serum tube) will be cryopreserved for later analysis.

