### 9.5 EFFICACY ANALYSES

#### 9.5.1 PRIMARY ENDPOINT ANALYSIS

The median and interquartile range (25th centile – 75th centile) is reported for anti-dsDNA antibody titers at baseline and at Week 12, i.e. 4 weeks after the last daratumumab injection. The change in between the two assessments is not tested in a confirmatory manner because of the exploratory study design. The median change is reported with its 95% confidence interval.

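### The sample-size claim of 80% power with 5 patients is false for the exact two-tailed Wilcoxon signed-rank test; at least 6 evaluable patients are needed

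*Protocol*

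**What the plan says.** Section 9.2 states: "A sample size of 5 patients is necessary to show a significant reduction in anti-dsDNA antibodies by a two-tailed Wilcoxon signed-ranked test". The comparison is of baseline with Week 12, and the stated conditions are "assuming a statistical power of 80% and a type one error rate of 5" per cent. The effect size of 2.1 comes from two patients treated under compassionate use, with a mean fall of 250 IE/ml and an SD of 121. A drop-out allowance of 50%, described as conservative, turns 5 into 10 enrolled. The synopsis repeats the claim ("A sample size of 5 patients is necessary to show a significant reduction in anti-dsDNA antibodies") and words the power as at least 80%.

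The analysis sections differ in tone. The synopsis says: "No confirmatory hypothesis test will be performed due to the exploratory study design". Section 9.5.1 likewise plans no confirmatory test and adds: "The median change is reported with its 95% confidence interval". Section 9.3 puts all enrolled patients in the main analyses, with a modified intention-to-treat analysis and a complete-case sensitivity analysis alongside. Section 9.4 fills missing efficacy values by last observation carried forward (LOCF). Section 3.1.1 and section 9.2 still describe the aim as a significant reduction; the primary objective in the synopsis does not use that word.

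**The concern.** The signed-rank test has a discrete null distribution, and with very few pairs its smallest attainable p-value can exceed 5%. If that is so at n = 5, the paragraph credits the design with a power it does not have. The enrolment target inherits the problem, because 10 is built to leave 5 evaluable patients, a number at which the named exact test cannot succeed. This paragraph is also the only numerical justification in section 9.2 for treating 10 patients.

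**Working it through.** **Inputs (section 9.2).** Mean fall 250, SD 121, two-sided alpha 0.05, power 80%, drop-out 50%, stated evaluable n = 5. Effect size d = 250/121 = 2.066, which the protocol rounds to 2.1.

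**1. Reproducing the plan's figure.** The usual software approximation treats the signed-rank test as a t-test on n × ARE observations, where ARE is the asymptotic relative efficiency. It uses a noncentral t with df = n × ARE − 1 and noncentrality d × √(n × ARE).

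- ARE = 3/π (normal parent), d = 2.066: power 73.8% at n = 4 and 90.2% at n = 5.
- ARE = 0.864 (minimum), d = 2.066: power 63.9% at n = 4 and 84.0% at n = 5.
- With d = 2.1, the power at n = 5 is 91.0% and 85.0% respectively.

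So 5 is the smallest n on this approximation, and 5/(1 − 0.5) = 10 follows. A paired t-test calculation also gives 5 (77.9% at n = 4, 92.4% at n = 5), but that is not the test named.

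**2. The exact test.** With n pairs there are 2^n equally likely sign patterns under the null hypothesis. The smallest two-sided p-value, reached when every change has the same sign, is 2/2^n. At n = 5 this is 2/32 = 0.0625. The 5% rejection region is empty, so the power is 0% whatever the effect size or distribution.

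At n = 6 the minimum is 2/64 = 0.03125, and the test rejects only if all six changes share a sign. For normal changes the power is therefore about Φ(2.066)^6 = 0.889. Larger n were simulated with normal changes, 400,000 samples each.

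| n | Smallest exact two-sided p | Exact power, d = 2.066 | Coverage of minimum to maximum, 1 − 2 × 0.5^n |
|---|---|---|---|
| 5 | 0.0625 | 0% | 93.75% |
| 6 | 0.03125 | 88.9% | 96.9% |
| 7 | 0.0156 | 98.9% | 98.4% |
| 10 | 0.00195 | above 99.9% | 99.8% |

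**3. Normal approximation at n = 5, all titres falling.** The rank sum has mean 5 × 6/4 = 7.5 and variance 5 × 6 × 11/24 = 13.75, so its SD is 3.708. Without continuity correction z = 7.5/3.708 = 2.02 and p = 0.043. With correction z = 7/3.708 = 1.89 and p = 0.059. The uncorrected version does declare significance, but it does so for the two all-same-sign patterns, so its true type I error is 2/32 = 6.25%, above the stated 5%.

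**4. Drop-out.** Six evaluable out of 10 enrolled tolerates 1 − 6/10 = 40% loss. Keeping 50% would need 6/0.5 = 12 enrolled.

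**5. The interval in the primary analysis.** With 10 patients, the 2nd to 9th ordered changes cover the median with probability 1 − 2 × (1 + 10)/1024 = 97.9%, so an exact interval of at least 95% is available.

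**6. Fragility of the effect size.** An SD from two patients has one degree of freedom. Assuming normality, its 95% interval runs from about 54 to about 3,860 IE/ml. At illustrative effect sizes of 1.5 and 1.0, exact power is 66% and 36% at n = 6, and 98% and 79% at n = 10.

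**The case against.** The strongest reply is that nothing in the analysis depends on the flawed test. The study is exploratory and no confirmatory test is planned. The primary analysis uses every enrolled patient with LOCF. Section 3.2.3 schedules anti-dsDNA at Weeks 3, 5, 7 and 9, so most patients who leave before Week 12 would have a post-baseline value to carry forward. At n = 10 and the plan's effect size, exact power exceeds 99.9%. Nor is 5 an arithmetic slip: it reproduces from the stated inputs. All of this stands, and it limits the consequence. It does not make the sentence in section 9.2 true. That paragraph inflates for drop-out, so it counts on 5 evaluable patients, not on 10 partly imputed ones.

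Four stronger readings are tempting, and the documents do not support them.

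- *The primary confidence interval cannot be produced at 50% drop-out.* Sections 9.3 and 9.4 keep all enrolled patients in that analysis. Only the complete-case analysis, or the modified intention-to-treat analysis after exclusions, could fall to 5 or fewer.
- *No 95% interval for a median exists at n = 5.* This holds only for exact distribution-free intervals. Section 9.5.1 names no method, and that choice may sit in the statistical analysis plan.
- *The trial will probably finish with 5 or fewer completers.* If each of 10 patients left independently with probability 0.5, the chance would be 638/1024 = 62%. But the protocol offers 50% as a conservative allowance, not as each patient's risk.
- *The drug-concentration assay hangs on this test.* Section 7.5 makes it conditional, "under the premise that the primary endpoint will be achieved", without a criterion. That is a separate question and does not follow from the n = 5 error.

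**Conclusion.** Wrong as written, with a limited consequence. For the exact two-tailed signed-rank test at 5%, 5 evaluable patients give 0% power, not 80%. This needs no assumption about effect size, SD or distribution, and zero changes among the five could only raise the minimum p-value. The uncorrected normal approximation does not rescue the claim, because it breaches the stated error rate. The correct minimum is 6 evaluable patients. The accompanying 89% power does assume normal changes and an effect size of 2.07 taken from two patients, so it is weakly supported. The fault affects the sample-size justification and the drop-out allowance built on it. It could also matter for a complete-case or modified intention-to-treat analysis left with 5 or fewer patients. The planned primary estimate and its interval are untouched.

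**What to change.** Change section 9.2 and the matching synopsis text in one of two ways.

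- **Keep a power statement.** State that at least 6 evaluable patients are needed for the exact two-sided signed-rank test at 5%, with power of about 89% at an effect size of 2.07 derived from two patients, and that enrolling 10 tolerates 40% loss.
- **Drop the power statement.** Justify 10 patients by the precision of the median change, which fits the descriptive analysis in section 9.5.1. Remove the word 'significant' from sections 3.1.1 and 9.2 and from the synopsis sample-size text.

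The second option is more consistent with the rest of the protocol and avoids leaning on an SD from two patients.

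In either case, add that if a complete-case or modified intention-to-treat analysis has 5 or fewer patients, the minimum-to-maximum interval is reported with its actual coverage, 1 − 2 × 0.5^n: 93.75% at n = 5, 87.5% at n = 4, 75% at n = 3.

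The cost is wording only. The downside of the first option is a lower tolerated drop-out, 40% instead of 50%; keeping 50% would mean enrolling 12. The second option gives up the power claim and needs no extra patients.
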